### Sample Size and Statistical Analysis

#### Sample Size Consideration

Primary analysis will involve the comparison of 2 group means. In addition, no interim analysis will be conducted. Therefore, group sample sizes of 37 (ie, 74 in total) are necessary to achieve 80% power to reject the null hypothesis of equal means when the population mean difference for State anxiety score is 5 with an SD for both groups of 7.47 [28] and a significance level (Cronbach α) of 5% using a 2-tailed *t* test. The SD for both groups varied from 4.61 to 7.47 [28]. To be conservative, we chose 7.47. On the basis of data from the medical imaging registry, the attrition rate was approximately 24%. Assuming a similar attrition rate, 98 participants (49 per group) will be required. The sample size calculation was performed using PASS Software (version 12.0; NCSS Statistical Software).

#### Statistical Analysis

Analyses will be conducted using SAS statistical analysis software (version 9.4; SAS Institute Inc). Descriptive statistics will be conducted for sociodemographic and clinical variables and presented by treatment group.

##### Primary Outcome Analyses

An analysis of covariance (ANCOVA) adjusted for age, sex, baseline (T0) Trait anxiety score measurement, and baseline State anxiety score measurement will be used to assess the mean difference in State anxiety scores on the STAIC-State between the experimental and the control groups at T2. Analyses will be carried out according to the intention-to-treat principle, with a significance level (Cronbach α) of .05.

##### Secondary Outcome Analyses

An ANCOVA adjusted for age, sex, and baseline anxiety score measurement will be used to assess the mean difference in anxiety scores on the CFS, between the experimental and the control groups at T2. To assess the mean difference in the sense of presence in VR and engagement into the game (GRS), between the experimental and the control groups at T1, an ANCOVA adjusted for age and sex will also be conducted. We will use a linear mixed model to estimate the effect of the treatment on the changes in heart rate over all assessment time points. This analysis will be adjusted for age, sex, and baseline heart rate. Differences between arms for levels of satisfaction of parents, children, and health care professionals (T2) as well as the overall procedure time will be assessed using (2-tailed) *t* tests or nonparametric Mann-Whitney *U* tests if data are nonnormal. A chi-square test or Fisher exact test will be conducted to compare dichotomous variables including the occurrence of side effects, the number of rescheduled MRI examinations, and the use of sedation in each group.

Adverse events and serious adverse events (if any) will be reported using the Medical Dictionary for Regulatory Activities terminology, and their proportions will be compared between the groups.

To help develop the predictability algorithm, the head deviations and other physiological data will be analyzed. An algorithm based on those deviations will be developed prospectively as the study progresses to evaluate the success of the MRI procedure in the intervention context and offer useful predictability inputs in preparation for the real MRI examination. No existing algorithms specific to the study were found. The physiological data will also help create a time sequence that could be matched with the information that will be extracted from the intervention. At the end of the session, it will be possible to see if, for example, a movement of the patient is generally triggered by an increase in stress as captured by the sensors. The result of the examination will then be compared with the data obtained during the intervention. The team will attempt to determine which variables correlate with the real-life outcome. Our hypothesis is that a patient who can follow the instructions well without any signs of anxiety captured by physiological parameters will have better results in the MRI procedure than a patient who has difficulty following the instructions or who shows signs of anxiety expressed through their physiological parameters.

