### Control Treatment

The usual care group will only receive the standard preparation, which comprises of an explanation of the MRI procedure given by the radiology technician as per the radiology department’s protocol. The research nurse will be able to complete any information should they find it incomplete or substandard.

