#### Measures of Primary Outcomes

The level of State anxiety (primary outcome) will be assessed using the State Scale of the STAIC-F questionnaire [25,26]. The STAIC-F (Multimedia Appendix 1 [25,26]) is a self-report instrument inspired by the State-Trait theory extended by Spielberger [27] that measures a momentary state of anxiety (state) and a stable tendency to experience anxiety (trait). The same author obtained internal consistency of coefficients of 0.87 for girls and 0.82 for boys [25]. The first 20 items constitute the situational (State) anxiety scale. The response “almost never” is graded 1, the response “sometimes” is graded 2, and the response “always” is graded 3, for a total score varying between 20 and 60 [26]. The next 20 items deal with Trait anxiety. The quotation is identical. A table is provided, which presents the average scores by age and sex. A score can be considered high when the child is ≥1 SD from the mean. It is typically completed in 8 to 12 minutes for initial evaluation, and subsequent evaluations typically require 5 to 7 minutes. The scale was developed specifically for use for children aged 9 to 12 years but can be used in younger children if the scale items are read out loud to them, as well as for older children [25]. Participants will rate their State-Trait anxiety with the French-Canadian version 40-item questionnaire (STAIC-F) in the waiting room (T0). The first 20 items, which correspond to situational anxiety, will be reassessed after the intervention (T1) and after the MRI examination (T2). Psychometric studies of the STAIC-F show excellent internal consistency coefficients of the State-Trait Anxiety Inventory for Children (STAIC) scales, with Cronbach α values of .89 and .88, respectively, and the test-retest reliabilities after a 6-month period were also similar to those of the original version, and the concurrent validity, assessed by the correlation with the Revised Children’s Manifest Anxiety Scale, was also found to be good [26]. A study investigated MRI examination–related anxiety in children using the English shortened-version of the STAIC scale for children aged 8 to 15 years [28], and 2 other studies examined MRI examination–related anxiety using the standard English STAIC scale for its robust psychometric properties for children aged 8 to 17 years and 12 to 18 years [29,30]. Considering the French-speaking population targeted in this study, the psychometrically sound properties of the French-Canadian version, and previous studies using the STAIC questionnaire to evaluate MRI examination–related procedural anxiety, we believe that it is justified to use this questionnaire in this study for children aged 7 to 17 years to evaluate their levels of anxiety.

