#### Secondary Outcomes

The secondary outcomes were (1) mean difference in the sense of presence and engagement (immersion) into the VR game between groups (T1), (2) the presence of head deviation during the intervention, (3) changes in physiological signs through biofeedback during the intervention, (4) satisfaction levels of parent (T2), (5) satisfaction levels of children (T2), (6) satisfaction levels of health care professionals (T2), (7) occurrence of side effects, (8) mean difference in total procedure time and frequency of rescheduling MRI examinations between groups, and (9) mean difference in Trait anxiety levels between groups.

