#### Measures of Secondary Outcomes

The secondary outcomes were measured as follows:

The sense of presence and engagement (immersion) in the VR game will be assessed using the Graphic Rating Scale (GRS) [38-40], a 7-item Likert-type scale tailored for VR interventions. Convergent validity among pairs of scores of the GRS with children aged 8 to 17 years was *r*=0.84 and test-retest reliability was 0.91 [40].The head deviation during the simulation will be measured continuously for the entire duration of the intervention through the positioning cameras, accelerometer, and gyroscopes in the headset.Physiological signs and biofeedback (heart rate, skin conductance, hand temperature, and muscle tension via an electromyogram) will be measured using the biofeedback device that will continuously capture and record physiological signs. The research nurse will note the heart rate measures at T0; immediately after T1; and at 1, 5, 10, and 15 minutes of the MRI procedure. Increased heart rates may indicate physiological arousal or may be a consequence of “positive stress” [41].Satisfaction levels of the parent will be assessed using a 0 to 10 numerical scale to answer the following question as recommended by Pediatric Initiative on Methods, Measurement, and Pain Assessment in Clinical Trials (PedIMMPACT) [42]: “Considering anxiety relief, side effects, and emotional recovery, how satisfied were you with the treatments your child received for anxiety?”Satisfaction level of the children will be assessed using a 0-to-10 numerical scale to answer the following questions: “How fun is the game?” “Did the game help you feel less scared during the MRI examination?” and “Will you recommend this game to other children who have to go through the same examination as you?”Satisfaction level of the health care professional will be assessed using a tailored questionnaire with a 4-choice response scale from strongly agree to strongly disagree for 7 items related to their level of satisfaction with the intervention and its effects on the procedure.Occurrence of side effects will be assessed and documented from enrollment until discharge.Procedural time and number of rescheduled MRI examinations will be noted in the clinical questionnaire.Trait anxiety level will be measured using the T scale of the STAIC-F.

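### VR presence and child satisfaction cannot be compared between arms because usual-care children never see the game, and Trait anxiety, measured only at T0, is a baseline variable listed as an outcome

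*Protocol article*

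**What the plan says.** **VR presence.** Secondary Outcomes lists first the "mean difference in the sense of presence and engagement (immersion) into the VR game between groups (T1"). Measures of Secondary Outcomes names the instrument, the GRS, as "a 7-item Likert-type scale tailored for VR interventions". Secondary Outcome Analyses sets an ANCOVA, adjusted for age and sex, on the "mean difference in the sense of presence in VR and engagement into the game (GRS), between the experimental and the control groups at T1".

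**Control exposure.** Control Treatment states: "The usual care group will only receive the standard preparation". That preparation is a verbal explanation from the radiology technician, which the research nurse may complete. The Objectives section likewise describes the comparison children as not exposed to the game.

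**Child satisfaction.** Measures of Secondary Outcomes gives three questions on a 0 to 10 scale: how much fun the game is, "Did the game help you feel less scared during the MRI examination", and whether the child would recommend it to others. Objectives includes a comparison of children's and parents' satisfaction between the groups. Secondary Outcome Analyses applies a t test or Mann-Whitney U test to "Differences between arms for levels of satisfaction of parents, children, and health care professionals (T2").

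**Trait anxiety.** Secondary Outcomes ends with ("9) mean difference in Trait anxiety levels between groups". Measures of Primary Outcomes says that the 40-item form, which holds the Trait items, is completed in the waiting room at T0, and then: "The first 20 items, which correspond to situational anxiety, will be reassessed after the intervention (T1) and after the MRI examination (T2"). Study Proceedings places the baseline anxiety measurements before the interventions. Primary Outcome Analyses uses the T0 Trait score as a covariate.

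**The concern.** A between-arm comparison estimates a treatment effect only if both arms can supply the measurement and if it is taken after treatment begins. The first two comparisons fail the first condition: a child who never wore the headset cannot rate immersion in the game, its fun or its help. The Trait comparison fails the second.

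The child-satisfaction gap matters most because it lies in data collection. If usual-care children are never asked a question they can answer, no later analysis plan can recover the answer, and the children's half of a stated objective is lost. The article also says under Design and under Criteria for Feasibility Assessment that nothing will change once the RCT starts, so the opportunity to correct this closes at that point.

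**Working it through.** The main check is to set the article's statements side by side. No effect size can be computed for the first two comparisons.

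**1. Can both arms supply the data?**

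| Planned comparison | Test named | What the item asks about | Can usual care answer? |
|---|---|---|---|
| GRS presence, T1 | ANCOVA (age, sex) | Immersion in the VR game | No |
| Child satisfaction, three items, T2 | t test or Mann-Whitney U | The game, in all three items | No |
| Parent satisfaction, T2 | t test or Mann-Whitney U | The treatments the child received for anxiety | Yes |

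With no control responses, the group term in the GRS ANCOVA is not estimable, and a two-sample test of child satisfaction has only one sample. The parent row shows that an arm-neutral wording already exists in the same section.

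**2. Is Trait anxiety measured after treatment?** The Trait items belong to the 40-item form given at T0. Only the 20 State items are repeated at T1 and T2. T0 precedes the interventions. There is therefore no post-treatment Trait score to compare.

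**3. What would a Trait comparison show if someone ran one?** Inputs: 49 per group and a two-sided 5% level, both from Sample Size Consideration. The group size reproduces:
- An exact two-sided t-test calculation for a difference of 5 and an SD of 7.47 gives 36.02, rounded up to 37 per group.
- 37 / (1 − 0.24) = 48.7, rounded up to 49 per group, or 98 in total.

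For a variable measured before randomisation takes effect, the expected difference between arms is 0. In SD units:
- Standard error of the difference = √(2/49) = 0.20.
- Smallest difference significant at 5% = t(0.975, 96 df) × √(2/49) = 0.40.
- Share of trials significant by chance = 5% by construction; a simulation of 20,000 trials gave 4.8%.

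These figures apply only if the comparison is tested. Secondary Outcome Analyses names no test for Trait anxiety.

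**4. How much of the plan is affected?** Two of the nine listed secondary outcomes (presence and child satisfaction) lack a control arm, and a third (Trait anxiety) is misplaced. Of the nine secondary objectives, the one on children's and parents' satisfaction is affected, and only in its children's half.

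**The case against.** **The failure would be visible and the core of the trial is sound.** An empty control column cannot go unnoticed at analysis, and VR presence can serve as a process measure on which no stated objective depends. The primary ANCOVA and the sample size do not rely on any of these variables. All of this stands and limits the weight of the point. It does not help child satisfaction, where noticing at analysis is too late.

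**A reader might infer a guaranteed significant result,** on the idea that usual-care children would be scored zero. The article does not support this. It nowhere says that control scores are set to zero or imputed, and it does not give the GRS scoring range. What follows from the text is that the comparison cannot be made.

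**A reader might infer that the plan tests Trait anxiety as efficacy, with a 5% risk of a false effect.** No such test is specified, so that figure is conditional. The supported statement is that a baseline variable is listed as an outcome.

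**Study Time Points says, without limiting it to the State items, that STAIC-F measures are taken at T0, T1 and T2.** That is looser wording. Measures of Primary Outcomes is specific that only the State items are repeated, and it describes Trait anxiety as a stable tendency.

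**A zero expected difference in Trait anxiety needs T0 to be completed before the child knows the allocation.** Study Proceedings puts T0 before the interventions but does not firmly place it before disclosure. This is fair. Self-report after disclosure could differ between arms, but that difference would still not be an effect of the preparation, which had not been given.

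**Experimental Treatment mentions a VR tour in the waiting area for patients and parents.** It appears under the experimental arm, and the control description and objectives exclude exposure to the game.

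**The questionnaire for health care professionals might be thought to share the defect.** Its seven items are not shown, so nothing can be concluded about them.

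**Conclusion.** The point holds for secondary outcomes. GRS presence and child satisfaction cannot be compared between arms as written, because usual-care children have no game to rate. The children's half of the satisfaction objective is therefore unanswerable with the planned items. Trait anxiety is a baseline characteristic and covariate listed as an outcome; a group difference in it would reflect baseline imbalance and not treatment.

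This rests on three readings: usual-care children do not play the game, the three child items are used as worded, and the specific statement that only State items are repeated governs over the looser one in Study Time Points. The primary inference, the sample size and the parent-satisfaction comparison are unaffected.

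**What to change.** Before the RCT starts:

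- **GRS and the three game items:** report them descriptively, with confidence intervals, in the IVR arm only, and remove the between-group wording from the outcome list and the analysis section.
- **Child satisfaction:** add one game-neutral 0 to 10 question for children in both arms, modelled on the parent item already in Measures of Secondary Outcomes, and apply the planned t test or Mann-Whitney U test to that question.
- **Trait anxiety:** delete it from the secondary outcomes; keep it as a baseline characteristic and as a covariate in the primary ANCOVA.

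The cost is one extra question per child and edits to the outcome list and analysis text. No additional participants are needed. The Results section reports no participant yet recruited to the clinical trial, and Design allows changes between the field test and the RCT, so the edits fit the article's own timetable.

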### Objectives

The primary research question concerns whether preprocedural interaction-enabled IVR game preparation will decrease MRI examination–related procedural anxiety for children undergoing an MRI procedure. The secondary objectives of the scientific clinical validation phases are as follows:

To determine whether preprocedural IVR game preparation is a feasible and acceptable nonpharmacological method to decrease MRI examination–related procedural anxiety.To determine whether children experiencing preprocedural IVR game preparation will have a slower heart rate before and during the MRI procedure than children not exposed to the IVR game preparation.To determine whether children experiencing preprocedural IVR game preparation will require lower need for sedation than children not exposed to the IVR game preparation before an MRI examination.To determine whether children experiencing preprocedural IVR game preparation will require rescheduling of the examination less often than children not exposed to the IVR game preparation before an MRI examination.To evaluate the occurrence of side effects with preprocedural IVR game preparation in comparison with children not exposed to the IVR game preparation before an MRI examination.To compare satisfaction levels of health care professionals between preprocedural IVR game preparation and usual care groups.To compare satisfaction levels of children and parents between preprocedural IVR game preparation and usual care groups.To compare overall procedure time required for an MRI examination between preprocedural IVR game preparation and usual care groups.To develop a predictability algorithm that will help identify which children will have better results in the MRI procedure after the IVR game preparation.

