### Inclusion Criteria

Children and their parents will be invited to participate in the study if they meet the following inclusion criteria: (1) aged 7 to 17 years; (2) required to undergo an MRI procedure; and (3) accompanied by a consenting parent or legal guardian who can understand, read, and write either French or English.

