### Measures and Outcomes

#### Sociodemographic and Clinical Questionnaire

Demographic and clinical characteristics will be assessed with parent reports filled out by the research nurse using the case report form and will include data on age, sex, ethnicity, reason for MRI imaging study, and history of imaging studies, including MRI, computed axial tomography scans, and x-ray examinations. Data such as name, dosage, and time of administration of anxiolytics taken 24 hours before the MRI examination will be collected. The questionnaire will also include a section describing the context of the procedure including adherence to the intervention, total procedure time, use of other nonpharmacological interventions, and the occurrence of side effects.

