### Study Proceedings (Clinical Validation Phases)

Participants will be identified through the radiology information system as having an appointment for an upcoming MRI procedure. Either the physician prescribing the MRI examination or the radiologist will have indicated certain patients as not needing sedation during the MRI examination and thus identified as eligible for this study. The research nurse will be notified by the radiology technologist and will contact the parents for recruitment a few days before the procedure. On the day of the appointment, parents will be approached to sign the consent if they still agree to the study. The child’s assent will also be obtained on the same day. Participants are informed of their assignment to either the preprocedural IVR game preparation or usual care group after randomization. Before initiation of the procedure, the research nurse will explain the intervention to the patient and install the IVR game preparation and start the video game program. Baseline measurements of anxiety will be taken before the interventions in the waiting room (T0).

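### Overall procedure time is compared without adjusting for the ordered examination although any MRI qualifies, so the test is valid but loses precision and may miss a modest saving if examination lengths vary widely

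*Protocol article*

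**What the plan says.** Procedure time is a named secondary objective in the protocol article, under Objectives: "To compare overall procedure time required for an MRI examination between preprocedural IVR game preparation and usual care groups". Secondary Outcomes lists it as a between-arm contrast: "mean difference in total procedure time and frequency of rescheduling MRI examinations between groups".

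Secondary Outcome Analyses fixes the test. Satisfaction scores "as well as the overall procedure time will be assessed using (2-tailed") t tests, with Mann-Whitney U as the fallback for nonnormal data. No covariate is named for either. In the same section the CFS, GRS and heart-rate analyses are adjusted; of heart rate it says "This analysis will be adjusted for age, sex, and baseline heart rate". The State anxiety analysis under Primary Outcome Analyses is adjusted too.

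Inclusion Criteria asks only that the child be "required to undergo an MRI procedure". Exclusion Criteria concerns fitness for VR and the sitting position. Study Proceedings adds that the prescribing physician or radiologist will have "indicated certain patients as not needing sedation during the MRI examination and thus identified as eligible for this study". None of these restricts body region, sequences or planned length.

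The Sociodemographic and Clinical Questionnaire records the "reason for MRI imaging study, and history of imaging studies", but the procedure-time analysis does not use it. Sample and Setting states that participants are found through their upcoming appointment in the radiology information system, so the examination has been ordered before recruitment.

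**The concern.** How long an MRI takes depends in part on what was ordered, and that is settled before randomization. An unadjusted two-sample test counts the spread in ordered length as noise. A variable of this kind is what covariate adjustment is for: known before allocation, plausibly strongly related to the outcome, and unaffected by the intervention.

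At stake is the precision of one secondary comparison. If examinations differ widely in length and the game saves only a few minutes, the planned test could give an inconclusive answer to a question the trial set itself, when the same participants could have given a sharper one.

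**Working it through.** **The plan's own figure.** Sample Size Consideration covers State anxiety only: difference 5, SD 7.47, two-sided 5%, power 80%. Noncentral-t power is 0.7997 at 36 per arm and 0.811 at 37 per arm, so 37 is the smallest number reaching 80%. Inflating for 24% attrition, 37/0.76 = 48.7, or 49 per arm, which agrees with "98 participants (49 per group) will be required". The number expected to be analysed is therefore 37 per arm, with 49 as the ceiling.

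**Inputs for procedure time.** The documents give no mean, SD, expected saving or spread of ordered lengths. Assumed here:
- residual SD (within a given ordered examination): 8 min
- SD between ordered examinations: 5, 10 or 15 min
- true saving: 5 or 10 min

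**Formulas.**
- Unadjusted total SD = sqrt(residual SD² + between-examination SD²).
- Standard error = SD × sqrt(2/n), with n per arm.
- Power = two-sided noncentral t with 2n − 2 degrees of freedom and noncentrality = saving / standard error.
- The adjusted analysis uses the residual SD alone. This assumes that the examination variable captures all between-examination variation, so adjusted power is an upper bound.

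**One case in full.** With a between-examination SD of 10, total SD = sqrt(64 + 100) = 12.8 min. At 37 per arm the standard error is 12.8 × sqrt(2/37) = 2.98 min, noncentrality for 5 min is 5/2.98 = 1.68, and power is 38%. With full adjustment the standard error is 8 × sqrt(2/37) = 1.86 min, noncentrality is 2.69, and power is 76%.

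**Power for a 5-min saving, residual SD 8 min**

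| Between-examination SD (min) | Total SD (min) | Unadjusted, 37/arm | Unadjusted, 49/arm | Adjusted (upper bound), 37 / 49 per arm |
|---|---|---|---|---|
| 5 | 9.4 | 61% | 74% | 76% / 86% |
| 10 | 12.8 | 38% | 48% | 76% / 86% |
| 15 | 17.0 | 24% | 30% | 76% / 86% |

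**Power for a 10-min saving, same residual SD.** Unadjusted power is 99%, 91% and 70% at 37 per arm, and about 100%, 97% and 82% at 49 per arm. Adjusted power is about 100%.

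**Sensitivity to the residual SD.** Take booked slots of 30, 45 and 60 min in equal shares (assumed). The between-examination SD is sqrt((15² + 0 + 15²)/3) = 12.25 min. For a 5-min saving at 37 per arm:

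| Residual SD (min) | Unadjusted | Adjusted (upper bound) |
|---|---|---|
| 8 | 31% | 76% |
| 15 | 20% | 29% |
| 20 | 15% | 19% |

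Adjustment gains in every row, but once variation unrelated to the booked examination dominates, it no longer rescues the comparison. These powers are for the t test; the Mann-Whitney fallback was not computed.

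**The case against.** The planned test is conventional and valid. Allocation is random, the between-examination variance is already in the standard error, and the error rate is controlled. Procedure time shares one entry in a list of nine secondary outcomes, and the trial is sized for State anxiety alone. The satisfaction scores are also compared without covariates, and no analysis in the article adjusts for examination type, so procedure time has not been singled out. Heart rate and the CFS have a baseline value to adjust for, which procedure time lacks. All of this stands and limits the weight of the point. None of it removes the loss of precision.

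Three stronger readings are tempting, and the documents do not support them.

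- A reader might infer that examination length swamps the comparison and that a real saving will probably be missed. That needs a wide mix of examinations and a small saving, and the article gives neither figure. With a between-examination SD of 5 min, or a saving of 10 min, it mostly fails.
- A reader might treat chance imbalance in examination mix as a further harm, or as bias. It is the same noise, which the unadjusted standard error already counts.
- A reader might think that the patient-turnover claim in the Discussion depends on this test. The Clinical Trial section there argues turnover from portability, home use and lower on-site staffing, not from the procedure-time comparison.

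Two further cautions stand. Sample and Setting attributes 48 of 193 procedures to delays and repetitions. If that time counts toward the outcome, the residual SD could be well above 8 min and the gain smaller. The article also does not say that the radiology information system holds slot length in usable form.

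**Conclusion.** The point holds as a matter of efficiency. The article fixes an unadjusted comparison of an outcome that depends in part on a pre-randomization variable, leaves the range of that variable open, and does not use it. The estimate stays unbiased and the test valid.

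The size is conditional. With a residual SD of 8 min and a 5-min saving, the most that adjustment could add at 37 per arm is 15 percentage points when the between-examination SD is 5 min (61% to 76%) and 52 points when it is 15 min (24% to 76%). The gain is negligible for a large saving with a narrow mix, and small when other sources of delay dominate. It is a cheap improvement to a secondary analysis and has no bearing on the primary result.

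**What to change.** In Secondary Outcome Analyses, take procedure time out of the sentence on t and Mann-Whitney tests. Analyse it with a linear model on arm, ordered examination category, age and sex. Booked slot length can replace the category if the radiology information system holds it. Report the adjusted mean difference with a 95% CI, using robust or bootstrap standard errors to deal with skewness. This also gives the mean difference that Secondary Outcomes promises, which a Mann-Whitney test does not.

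Add the examination category (or slot length) to the case report form and record it before allocation, so that it cannot be affected by the arm. Keep the categories few, since each one uses a degree of freedom with about 74 evaluable children.

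The cost is one extra data field, one sentence of analysis text and a few degrees of freedom. No additional participants or visits are needed.
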